### Intervention

The cognitive rehabilitation program will be based on the protocol of a frequently used meta-cognitive strategy approach applied in many rehabilitation centers in the Netherlands (i.e., “Niet Rennen Maar Plannen”). In cooperation with the creators of this protocol, we will adapt it for work-related cognitive problems and for online use. Patients and professionals will evaluate the adapted version of the protocol in several stages throughout its development. Both individual sessions and focus group interviews will be organized to obtain feedback, which will be used to evaluate and improve both content and user-friendliness of the adapted version of the intervention. The program will consist of several modules that can be used in a flexible way, depending on the specific individual problems and goals. As part of this study, therapists have undergone additional training in issues related to cancer-related cognitive impairment and problems occupationally active cancer survivors might experience at work. In both intervention arms, participants will receive access to a secured personal webpage, where all content relevant to the treatment sessions can be obtained. The basic and extensive intervention arms differ with regard to (1) therapy guidance (i.e., absent in the basic arm and present throughout the whole program in the extensive arm) and (2) intervention content. Table 1 shows an outline of the intervention content of the basic and the extensive cognitive rehabilitation program. The number and duration of sessions of both intervention arms may vary according to the individual needs and preferences of the participants, in line with the original face-to-face program on which the interventions are build. Therefore, there is no fixed number or duration of sessions in both intervention arms.

**Table 1 Tab1:** Outline intervention content

Modules	Content	Basic cognitive rehabilitation	Extensive cognitive rehabilitation
1. Psychoeducation	▪ Review current knowledge about cancer related cognitive impairment ▪ Learning how to identify “at risk” situations (at work) where cognitive failures arise	X X	X X
2. Fatigue-management	▪ Coping with fatigue (at work)	X	X
3. Cognitive behavioral therapy	▪ Coping with behavioral and emotional consequences of cognitive impairment (at work)	X	X
4. Communication	▪ Learning how to disclose your cognitive problems to colleagues	X	X

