#### Waiting list control group

Participants in the waiting list control group will be offered the opportunity to follow the basic cognitive rehabilitation program after completion of the 26-week follow-up measurement.

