#### Mediation and moderating measures

Fatigue (SF-36) and coping (CERQ) are considered mediators and will be assessed through self-report questionnaires [42, 43]. Neuropsychological functioning is considered a moderator and will be measured using a self-administered online neuropsychological test battery (ACS) [44]. Other moderators are work involvement (WIS) [45], job characteristics (JCQ) [46], depression and anxiety (HADS) [47], and treatment utilization (Log-data of the online program).

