In this study, GAS will be used as the primary study endpoint, evaluating between-group differences over time in GAS scores. The GAS scores will be calculated according to published scoring algorithms (see the “Methods/design” section). To evaluate intra-individual differences in the trajectory of change over time for the primary outcome, we will use a growth curve modeling approach with random intercept and slope. This approach takes into account the within- and between-person variability and deals adequately with missing data [51]. Both linear and quadratic effect of time will be modeled to determine if an initial improvement or deterioration in the outcome was followed by a deceleration of this change over time. Appropriateness of the final model (with or without quadratic effect) will be determined based on model fit statistics: the Bayesian information criterion [52] and the Akaike information criterion [53]. In all analyses, the control group will be the reference group. Furthermore, moderation analysis will be conducted to determine whether the interventions have a differential effect among the subgroups classified as cognitive impaired yes or no (measured by ACS) at baseline. Baseline differences will be accounted for in the model. In case of non-ignorable dropout, we will correct the model for different patterns of missing values [54]. All analyses will be done on an intention-to-treat basis. Furthermore, as a secondary analysis, per-protocol analyses will be performed on patients who met criteria for minimal compliance (i.e., at least 4 logins into the online program) with the intervention(s). Differences in mean change scores over time between the intervention groups and the control group will be accompanied by effect sizes. Effect sizes of 0.2 are considered small, 0.5 moderate, and 0.8 large [55]. Effect sizes of approximately 0.5 are considered to be clinically relevant [56].

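### The secondary per-protocol analysis compares login-selected programme patients with an unselected waitlist arm, so it is not a randomised comparison and is open to selection bias, probably but not certainly towards the programmes

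*Protocol article*

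**What the plan says.** All references are to the protocol article.

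- **Main basis (Statistical analysis).** "All analyses will be done on an intention-to-treat basis".
- **Per-protocol set (same section).** It is introduced with the words "Furthermore, as a secondary analysis, per-protocol analyses will be performed", and the set is fixed by a login count: "per-protocol analyses will be performed on patients who met criteria for minimal compliance (i.e., at least 4 logins into the online program".
- **Comparator (same section).** "In all analyses, the control group will be the reference group".
- **Programme access (Intervention).** "In both intervention arms, participants will receive access to a secured personal webpage". The same section lets the number and length of sessions follow individual needs and preferences, with no fixed number.
- **Waitlist (Waiting list control group).** Its participants "will be offered the opportunity to follow the basic cognitive rehabilitation program after completion of the 26-week follow-up measurement".
- **Moderators (Mediation and moderating measures).** The list includes "treatment utilization (Log-data of the online program".
- **Safeguards (Statistical analysis).** Baseline differences enter the model, and non-ignorable dropout is to be handled by missing-data patterns. No rule defines compliance in the waitlist arm, and no method is named for the selection that the login rule creates.

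**The concern.** Login count is a behaviour that follows randomisation. Patients who log in at least 4 times may differ from the rest in motivation, fatigue or severity of problems. In the waitlist arm the patients who would have logged in that often cannot be identified. The contrast then mixes the programme effect with the prognostic difference between users and an unselected group.

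A per-protocol result is easily taken as the effect in people who used the programme. As defined, it could show a benefit where there is none, or hide one. Incomplete use is foreseeable, because the protocol fixes no number of sessions.

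The same login data are also named as a moderator. A moderator of the programme-versus-control effect needs a value in both arms, and utilisation has none in the waitlist arm during follow-up.

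**Working it through.** **Step 1: who can be selected.** The two programme arms have access during follow-up. The waitlist is offered the "basic cognitive rehabilitation program after completion of the 26-week follow-up measurement", so no waitlist patient can meet or fail the rule before the last measurement. Applied literally to all arms, the rule would leave no controls. Since the control group is the reference in all analyses, the only workable reading keeps the whole waitlist and trims the programme arms. The text does not say this in words; it follows from the three sections together.

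**Step 2: do the stated safeguards repair it?** Adjustment for baseline differences cannot remove selection on unmeasured motivation or on events after randomisation. The dropout correction concerns missing outcomes, whereas here patients with observed outcomes are left out on purpose.

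**Step 3: size, for illustration.** The plan gives no figure for the per-protocol set, so there is none to reproduce. Inputs:

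- From Sample size calculation: 87 per arm, about 20% attrition and a design effect of d = 0.4. Evaluable patients per arm: 87 × 0.80 = 69.6, taken as 70.
- Assumed: the share c with at least 4 logins is 0.6, 0.7 or 0.8.
- Assumed: without any programme, users would score δ = 0.3 or 0.5 SD better than non-users.
- No true effect, outcome SD of 1, two-sided 5% test.

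The mean of a whole arm is c × (users) + (1 − c) × (non-users). The users' mean therefore exceeds the arm mean by (1 − c) × δ, which is the bias against an untrimmed waitlist. The standard error is √(1/(70c) + 1/70).

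| c | SE | bias, δ = 0.3 | rejection | bias, δ = 0.5 | rejection |
|---|---|---|---|---|---|
| 0.6 | 0.195 | 0.12 | 9.4% | 0.20 | 17.6% |
| 0.7 | 0.186 | 0.09 | 7.7% | 0.15 | 12.7% |
| 0.8 | 0.179 | 0.06 | 6.3% | 0.10 | 8.6% |

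Example for c = 0.6, δ = 0.5: 0.4 × 0.5 = 0.20, and 0.20/0.195 = 1.02. P(Z > 1.96 − 1.02) + P(Z < −1.96 − 1.02) is about 0.176.

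Against d = 0.4, the bias is 0.06/0.4 = 15% to 0.20/0.4 = 50%.

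**Step 4: a second model, including the other sign.** Let r be the correlation between login propensity and untreated outcome, and let c again be the share selected. Under normality the bias is r × φ(z)/c, where φ is the standard normal density and z the cut-off that a share c exceeds.

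| c | r = −0.2 | r = 0 | r = 0.2 | r = 0.3 | r = 0.5 |
|---|---|---|---|---|---|
| 0.8 | −0.07 | 0 | 0.07 | 0.10 | 0.17 |
| 0.6 | −0.13 | 0 | 0.13 | 0.19 | 0.32 |

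Simulation with 87 per arm and 5,000 runs gave the same mean differences to within 0.01 SD. The rate of false findings in favour of a programme (nominal 2.5%) was 6%, 9% and 20% at c = 0.8 for r = 0.2, 0.3 and 0.5. At c = 0.6 it was 11%, 20% and 46%. With r = −0.2 it fell below 1%.

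The two models agree. Dividing the bias by (1 − c) gives the implied gap between users and non-users: 0.07/0.2 = 0.35 SD for r = 0.2, and 0.10/0.2 = 0.5 SD for r = 0.3.

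**The case against.** The strongest reply is that this is a declared secondary analysis beside an intention-to-treat analysis. Adding a minimal-exposure set is conventional, and every such set gives up the protection of randomisation. That stands in part. The primary conclusion does not depend on this analysis, and the protocol does not say that it will carry an efficacy claim. It does not make the contrast sound: the protocol fixes the threshold and the reference group and offers nothing for the selection.

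Three stronger readings are tempting, and the documents do not support them.

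- **That the contrast is biased towards the programmes as a matter of fact.** Nothing in the protocol links logins to prognosis. Because use may follow need, low users may have milder problems or reach their goals early, which would reverse the sign. Baseline adjustment could also shrink the bias.
- **That the moderator lists contradict each other.** Secondary study parameter(s) names baseline scores on four instruments and is silent on utilisation. It does not say that the list is complete, and silence in a condensed article is not a contradiction.
- **That the unblinded goal scoring, done by patient and therapist together, makes the per-protocol rule worse.** It affects the intention-to-treat comparison as well, so it is not a fault of this rule.

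It is also fair to say that both programme arms have login data, so an interaction of utilisation with basic versus extensive can be computed. It would not have a causal reading, and the difficulty against waitlist remains.

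**Conclusion.** The structural point holds. The login rule selects after randomisation, and in the programme arms only, so the per-protocol contrast with waitlist is not a randomised comparison. Bias towards the programmes is the likelier direction but is not established.

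Its size rests wholly on assumed inputs. It is 0.06–0.20 SD, with rejection in about 6–18% of null trials, if 60–80% comply and compliers would do 0.3–0.5 SD better anyway. It is zero if their prognosis is equal and reversed if it is worse. The intention-to-treat result is untouched.

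Treatment utilisation cannot moderate a programme-versus-control effect, because it arises after randomisation and has no value in the waitlist arm.

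**What to change.** 1. Estimate the effect in users as a complier-average causal effect, separately for each programme versus waitlist. Use randomisation as the instrument and at least 4 logins as treatment received, keep all randomised patients, and use the covariates of the primary model. If assignment has no effect at all, this estimate is centred on zero, so it remains a valid test of no effect.
2. State the exclusion restriction beside the result: assignment must have no effect in patients with fewer than 4 logins. This is doubtful in the extensive arm, where therapist guidance is not measured by logins. If assignment shifts such patients by e, the estimate is off by e × (1 − c)/c, which is 0.25e at c = 0.8 and 0.67e at c = 0.6. A positive e inflates the benefit.
3. If the simple per-protocol contrast is kept, label it non-randomised and exploratory.
4. Remove treatment utilisation from the moderator list and report the log data under dosage in the process evaluation.

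The cost is a change of wording and one further model on data already planned. The interval widens. With 70 per arm the intention-to-treat SE is √(2/70) = 0.169; divided by c (treated as known) it is 0.211 at c = 0.8 and 0.282 at c = 0.6. The simple contrast has 0.179 and 0.195, so the complier interval is about 18% to 44% wider.

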### Sample size calculation

This longitudinal study design will allow for testing of the main effect of the intervention over time, with the GAS score as the primary outcome measure. With a sample size of 65, and an alpha = 0.05, the study will allow for an attrition rate of approximately 20% and have 80% power to detect an effect size of *f* = 0.2 (equivalent to Cohens *d* = 0.4) for the main effect of the intervention between both the basic and extended cognitive rehabilitation treatment group versus the waitlist control group (first hypothesis). To perform subgroup analysis, used to test our second hypothesis, sample size should be inflated fourfold [50]. Therefore, we strive for a sample size of 261, with 87 patients in each group.

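### The secondary per-protocol analysis selects on logins that only the programme arms can have, so its contrast with the waitlist is not a randomised comparison

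*Protocol article*

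**What the plan says.** All of this is in the protocol article.

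- **Statistical analysis.** The main basis is clear: "All analyses will be done on an intention-to-treat basis". A further analysis, described as secondary, is then added: "per-protocol analyses will be performed on patients who met criteria for minimal compliance (i.e., at least 4 logins into the online program". The comparator is fixed for everything: "In all analyses, the control group will be the reference group". On adjustment, the section says "Baseline differences will be accounted for in the model". It also plans a correction for missing-value patterns if dropout is non-ignorable.
- **Intervention.** Programme access belongs to the programme arms: "In both intervention arms, participants will receive access to a secured personal webpage". Use is not standardised: "The number and duration of sessions of both intervention arms may vary according to the individual needs and preferences of the participants".
- **Waiting list control group.** Controls "will be offered the opportunity to follow the basic cognitive rehabilitation program after completion of the 26-week follow-up measurement". They have no logins while T1 and T2 outcomes are collected.

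The article does not say how waitlist patients enter the per-protocol set.

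**The concern.** Reaching four logins happens after randomisation, and only two of the three arms can do it. Taken literally, the rule removes every waitlist patient and leaves no reference group. The only workable reading keeps the whole waitlist and drops low users from the programme arms. The groups compared are then no longer those that randomisation made alike.

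If the dropped patients would have done worse anyway, the remaining programme patients look better even when the programme does nothing. The result could then be read as confirming the intention-to-treat finding when part of it is selection. The comparison between the two programmes may be affected too. They differ in content and guidance, so four logins may select different kinds of patients in each.

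**Working it through.** **Reading the rule.** Set side by side, the Intervention, Waiting list control group and Statistical analysis sections give zero waitlist logins before T2, a threshold of four, and the waitlist as reference. The exclusion can act on the programme arms only.

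**Does the plan already repair this?** Adjustment for baseline differences removes only what measured baseline variables explain. It does not reach unmeasured motivation, or workload and fatigue that arise later. The missing-pattern correction addresses dropout, not patients excluded for few logins. The secondary status protects the primary result but does not make this contrast randomised.

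**Size.** The plan states no figure for this analysis, so there is none to reproduce.

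Inputs from the protocol article:
- 87 per arm and about 20% attrition (Sample size calculation), giving 87 x 0.8 = 69.6, about 70 analysed per arm
- design effect d = 0.4 (same section)
- GAS T-score SD of 10 (Primary outcome measure)
- 0.5 as the clinically relevant effect size (Statistical analysis)
- alpha 0.05, taken here as two-sided because sidedness is not stated

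Assumptions not in the documents:
- a share a = 0.7 to 0.8 reaches four logins
- those who do have outcomes g = 0.3 to 0.5 SD better than those who do not, whatever the programme does

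With no programme effect, the compliers' mean exceeds the whole-arm mean by g - a x g, so:

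- bias = (1 - a) x g
- SE = sqrt(1/(70a) + 1/70), in SD units
- rejection rate = P(Z > 1.96 - bias/SE) + P(Z < -1.96 - bias/SE)

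| a | g | bias (SD) | SE | rejection under no effect |
|---|---|---|---|---|
| 0.8 | 0.3 | 0.2 x 0.3 = 0.06 | 0.179 | 0.063 |
| 0.8 | 0.5 | 0.2 x 0.5 = 0.10 | 0.179 | 0.086 |
| 0.7 | 0.3 | 0.3 x 0.3 = 0.09 | 0.186 | 0.077 |
| 0.7 | 0.5 | 0.3 x 0.5 = 0.15 | 0.186 | 0.127 |

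A bias of 0.06-0.15 SD is 0.6-1.5 GAS T points. It is 12-30% of 0.5 and 15-38% of 0.4.

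**Sign.** With g = 0 the bias is zero. With g = -0.3 to -0.5 it is -0.06 to -0.15 SD, and by symmetry the two-sided rejection rates are the same.

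**Check with another model.** Let engagement correlate r with outcome and drop the lowest share q of users from the programme arm only. The shift is r x phi(z_q)/(1 - q), where phi is the standard normal density and z_q the q-quantile. For q = 0.2 and r = 0.3 it is 0.3 x 0.280/0.8 = 0.105 SD. In 20,000 simulated null trials per setting, with 87 per arm before exclusion, that case rejected 10.4% of the time. Over q = 10-40% and r = 0.1-0.5 the rate ran from 5.2% to 48.2%. Intention-to-treat on the same data stayed between 4.7% and 5.6%.

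**Behaviour of the alternative.** With one-sided non-compliance, the complier-average estimate is roughly the intention-to-treat estimate divided by the share a who receive the programme. Under no effect it centres on zero. The interval widens by about 1/a, which is 1.25 at a = 0.8 and 1.43 at a = 0.7. If patients below the threshold gain an amount e0, the estimate is too large by (1 - a) x e0/a, that is 0.25 e0 or 0.43 e0. The threshold that defines receipt therefore matters.

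**The case against.** The strongest reply is that the analysis is already placed second to intention-to-treat, that no hypothesis in the Background is assigned to it, and that nearly any per-protocol comparison with an untreated control has this weakness. That bounds the importance and stands. It does not settle the point, because the article fixes both the login rule and the reference group, and together they yield either no control group or a one-sided filter.

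The second reply concerns direction. A reader might infer that the per-protocol result will always match or exceed intention-to-treat. The documents do not support that. Use follows individual needs and preferences, so low users may have milder problems or early success. In the extensive arm, strategy modules are assigned by cognitive profile and goals, so heavy use may mark greater impairment. Nor do they say that low users are the most tired or busiest patients, or that therapists prompt logins; guidance is described as discussing reflection and homework.

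Third, the size is assumed. Four logins is a low bar, so compliance may exceed 80%. If non-users are largely the patients who drop out, and similar patients leave the waitlist, few remain to exclude. Baseline adjustment would remove some of the gap. All of these shrink the bias.

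Fourth, a complier-average analysis with receipt set at four logins rests on a doubtful assumption. Programme content can be read in one to three logins, and guidance in the extensive arm can act whatever the login count. This stands and shapes the fix. Nor does the estimator add an independent test, since it rescales the intention-to-treat estimate.

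**Conclusion.** The concern holds for the secondary per-protocol contrasts with the waitlist: as planned, they are not randomised comparisons. Bias towards benefit is conditional on users having a better prognosis. Under 70-80% compliance and a 0.3-0.5 SD gap it is 0.06-0.15 SD, with 6-13% false positives. Both inputs and the sign are assumptions, and zero or reversed bias is compatible with the text.

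A reader might go further and doubt the trial's main conclusion. The documents give no ground for that, since the primary analysis keeps patients as randomised. The point merits a change to the plan because the remedy is cheap and a biased secondary result can be mistaken for corroboration.

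**What to change.** - As the secondary compliance analysis, estimate a complier-average causal effect for each programme against the waitlist. Use randomised arm as the instrument, keep all randomised patients, and include the cognitive-impairment factor used in the minimisation as a covariate.
- Define receipt as any programme use: at least one login, or any therapist session in the extensive arm. Do not count the goal-setting session before randomisation or the telephone GAS scoring, which all arms have.
- Show the 4-login definition as a sensitivity analysis.
- State the exclusion restriction under each definition: allocation has no effect on patients who do not meet the definition of receipt.
- If the per-protocol table is kept, state that all waitlist patients are retained in it and label it descriptive and non-randomised.

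The cost is a change of wording and one instrumental-variable model per programme. Log-data are already listed among the moderators, and therapist time per patient is already collected for the economic evaluation. The downside is a wider interval and an assumption that the data cannot test.

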#### Secondary study parameter(s)

We will calculate questionnaire scores according to published scoring algorithms. Missing values will be replaced by the average score of the completed items in the same scale for each participant, provided that at least 50% of the items in that scale have been completed. For the CSC-W DV, WAI, WRFQ, iPCQ, VBBA, and SF-36, the same growth curve modeling approach as described in the primary study parameter section will be used to evaluate between-group differences over time. In addition, we will test whether intervention effects are moderated by baseline scores on the ACS, WIS, JCQ, and HADS. Finally, we will explore the mediating effect of the (anticipated time-variant) variables fatigue (SF-36) and coping (CERQ) on the secondary outcomes.

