#### Basic cognitive rehabilitation program

The basic arm will consist of a brief cognitive training program without individual guidance throughout the intervention, which has to be completed in a period of 12 weeks.

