### Data collection

Participants will be followed for 6 months in total and will be invited to complete measurements at three time points (at baseline (T0), treatment endpoint at 12 weeks post-randomization (T1) and at 26 weeks post-baseline (T2)). Measurements will be performed via a secured website, for which a link will be sent by email. Intervention effectiveness will be measured in terms of work-related goal attainment and secondary outcome measures. Secondary analyses will be performed to explore moderating and mediating processes. An overview of measures and mediating and moderating processes in treatment is presented in Fig. 3. Detailed descriptions of these secondary study measures are provided in Table 2.

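### For the secondary questionnaires, choosing straight-line or quadratic time by BIC and AIC can shrink the T1 effect if the gain is reached by programme end and then held

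*Protocol article*

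**What the plan says.** Under Statistical analysis, the protocol article describes a "growth curve modeling approach with random intercept and slope". It adds that "Both linear and quadratic effect of time will be modeled", the purpose being to see whether an early change slows down later. The choice between the two is left to the data: "Appropriateness of the final model (with or without quadratic effect) will be determined based on model fit statistics". The two statistics named are BIC and AIC, with no order of precedence and no rule for disagreement. The text does not say whether the quadratic term is allowed to differ by arm.

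Under Secondary study parameter(s), "the same growth curve modeling approach as described in the primary study parameter section will be used" for the CSC-W DV, WAI, WRFQ, iPCQ, VBBA and SF-36.

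Data collection sets three visits: T0 at baseline, T1 at 12 weeks (named the treatment endpoint) and T2 at 26 weeks. The basic programme is one "which has to be completed in a period of 12 weeks", and the extensive programme has the same limit, so T1 coincides with programme end. Effect sizes are attached to between-arm differences in mean change.

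This point concerns the questionnaires that have a real T0 value. It does not concern the GAS model.

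**The concern.** With three fixed visits, a straight line allows only one shape: the change at week 12 must be 12/26 = 46% of the change at week 26. If a questionnaire improves during the programme and then stays level, that shape is wrong and the misfit falls on T1, the visit the plan calls the treatment endpoint. The quadratic can follow such a course, but only if it is selected and only if it may differ by arm.

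The selection is made outcome by outcome on the data being analysed, with two criteria of very different strictness. One questionnaire could be reported as linear and another as curved, so their T1 effects would not be comparable. Ordinary confidence intervals would also take no account of the selection step.

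**Working it through.** The plan gives no figure for criterion disagreement or for the T1 effect under a linear fit, so there is none to reproduce.

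**Inputs from the article.** Visits at 0, 12 and 26 weeks; 261 participants, 87 per arm; about 20% attrition; random intercept and slope. **Assumed, because the article gives none:** effect shape and size on the questionnaires, between-visit correlation, and the terms that the quadratic adds.

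**1. How far apart the criteria are.** If the quadratic adds time² and two arm-by-time² terms (three parameters):
- AIC penalty: 2 × 3 = 6.
- BIC penalty: 3 × ln(261) = 16.7 counting participants, or 3 × ln(783) = 20.0 counting 261 × 3 observations.

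Any likelihood-ratio statistic between 6 and 16.7 (or 20.0) makes AIC choose the quadratic and BIC the straight line.

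**2. What a straight line does to a plateau.** Take a true arm difference of 0, 1, 1 at weeks 0, 12, 26.
- Mean time = 38/3 = 12.67; sum of squared deviations = 338.67; sum of cross-products = 12.67.
- Slope = 12.67/338.67 = 0.0374 per week; intercept = 0.667 − 0.0374 × 12.67 = 0.193.
- Change from baseline to T1: 12 × 0.0374 = **0.45**.
- Fitted arm difference at T1: 0.193 + 0.449 = **0.64**; at T2: 0.193 + 0.972 = **1.17**.
- Baseline forced equal, unweighted least squares: slope = 38/820 = 0.0463, so T1 = **0.56**. In the mixed model, which weights by the within-person correlation, the corresponding figure is **0.47-0.50**.

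Simulated fits with a 0.40 SD plateau agree: 0.17-0.18 as change to T1, 0.19-0.20 with baseline constrained equal, and 0.25-0.26 as fitted arm difference. Three separate visit means recover 0.39-0.40.

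If the quadratic is common to all arms, the arm difference remains linear in time. Selecting that quadratic therefore does not repair T1. If the true effect is linear, the straight line loses nothing.

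**3. How often the criteria disagree.** Simulated with 300 trials per setting, 87 or 70 per arm, intercept/residual variances 0.5/0.5 or 0.7/0.3, random-slope SD 0.3:

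| True course | Disagreement |
|---|---|
| 0.4 SD plateau in both programmes, flat controls, arm-by-time² | 34-71% |
| 0.4 extensive and 0.2 basic plateau, arm-by-time² | 52-71% |
| 0.3 at T1, 0.4 at T2, arm-by-time² | 29-58% |
| 0.5 SD plateau, arm-by-time² | 7-56% |
| 0.4 SD plateau, one common time² term | 13-40% |
| Controls also rise 0.2 and level off | 0-34% |
| No effect, or a linear effect | 10-17% |

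A separate set (120 trials per setting, 87 per arm, 20% lost by T2, visit correlation 0.5-0.7, plateau 0.3-0.4 SD) gave 41-63%. BIC chose the straight line in 46-93% of trials and AIC in 5-29%.

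The last row of the table can be checked directly. With no curvature the likelihood-ratio statistic is about chi-square. For three terms, P(>6) − P(>16.7) = 0.112 − 0.001 = 11%. For one term, P(>2) − P(>5.56) = 0.157 − 0.018 = 14%.

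**The case against.** The strongest reply is that the plan already contains the remedy. It fits a quadratic precisely to detect a slowing of change, and at three visits a quadratic with arm interactions reproduces every arm's visit means. Consulting AIC and BIC together is common in growth-curve work, and which one prevails is the kind of detail a SAP or full protocol may settle. That last part stands: silence on the tie-break alone would not be a finding. But the data-driven selection is itself the stated method. One of its two candidates distorts the treatment-endpoint contrast under a course the article explicitly looks for.

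A reader might infer that a 12-week programme breaks the straight line by design. The article does not support this. Nowhere does it say that the gain is complete at T1 and flat afterwards, and strategies practised at work after the programme could give a steady rise.

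A reader might also infer that the criteria disagree in about half of all trials. That rate belongs to one family of assumptions; other plausible courses give far lower rates. The article's d = 0.4 refers to the GAS and not to these questionnaires.

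Nor is a halving of the T1 effect general. It needs the plateau and an estimate taken as change from baseline or with baselines constrained equal; the fitted arm difference loses about 36%. The article's wording on mean change favours the former, but does not say whether those changes are model-based or observed. Observed changes would not be altered by the selection.

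**Conclusion.** The concern holds conditionally. The secondary-outcome model is chosen separately for each questionnaire on the same data, by two criteria with penalties of 6 and about 16.7-20 if three terms are added. Neither the precedence nor the arm-by-time² terms are stated.

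If an effect is reached by T1 and held to T2, choosing the straight line, or a quadratic common to all arms, leaves about 45-50% of the T1 effect as change from baseline or with baseline constrained equal, and about 64% as fitted arm difference. A true 0.40 SD would then appear as roughly 0.18-0.20 or 0.26. With a truly linear effect there is no loss.

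Disagreement in roughly 35-70% of trials rests on an assumed 0.3-0.4 SD plateau, flat controls, arm-by-quadratic terms and assumed correlations. With no effect or a linear effect it is about 10-17%. The weakness in the rule does not depend on any one of these rates. It is confined to secondary outcomes and says nothing about the primary conclusion, but it should be corrected before analysis.

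**What to change.** For the secondary questionnaires with a T0 value, drop the AIC/BIC selection. Fit visit as a category (T0, T1, T2) with visit-by-arm terms, arm means constrained equal at T0 (or the baseline value as covariate) and an unstructured covariance. Report the arm difference at T1 and at T2 from that one model for every outcome. Keep the growth curve as a descriptive supplement.

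With three visits, visit-by-arm terms give the same mean structure as the full arm-by-quadratic model before the baseline constraint, so no shape that the plan can currently fit is lost. The change is to analysis wording only and needs no new data. The cost is two effects per programme in place of one slope, and slightly less power if the true course is exactly linear.
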